## Methods/design

The overall aim of the study is to assess the impact of the support groups on the sustainment of exclusive breastfeeding until the first 6 months after birth. More specifically we will:
Determine factors related to breastfeeding sustainment.Identify the motivators of breastfeeding interruption in infants during the first 6 months of life.Describe the main problems consulted by women in the breastfeeding support groups.Compare the strategies of face-to-face and virtual ante/postnatal sessions with only postnatal sessions regarding breastfeeding sustainment.Know the influence of these support groups on the perceived self-efficiency of breastfeeding.

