#### Secondary outcomes measurement

Differences between both groups with respect to the following:
***Sociodemographic outcomes:*** mother’s age, schooling level (without any studies, primary, secondary, University studies), marital status (single, married, divorced, widow), work status (self-employed, employed, unemployed), occupation, working hours/week, home country.***Breastfeeding outcomes:****Breastfeeding observation form (BREAST):* it is a tool developed by a WHO experts committee in 1992 [24], which collects the key points in order to assess a breastfeed through observation: body position (B), responses (R), emotional bonding (E), anatomy (A), suckling (S), and time spent suckling (T). In the Baby-Friendly Hospital Initiative (BFHI) strategy [27], it is specified that a complete breastfeed observation by an expert is essential for checking whether there is an appropriate transfer and for diagnosing the cause of possible difficulties, should there be any, for further resolution.*Breastfeeding Self-Efficacy:* a reduced version of the *Breastfeeding Self-Efficacy Scale-Short Form* (BSES-SF) [30] scale [26] which was validated in Spanish by Oliver-Roi et al. [26], and counts on 14 items grouped in only one dimension. It is a one-dimensional, self-completed scale of 14 items, positively presented and preceded by the sentence ‘I always can’. For scoring, it has a Likert-type scale from 1 to 5, where 1 indicates ‘not sure at all’ and 5 indicates ‘very sure’. Higher scores mean higher self-efficacy levels for breastfeeding. The BSES-SF Spanish version’s reliability, measured with the Cronbach alpha coefficient, is 0.92. It is a valid and reliable measure, successfully adapted into diverse cultural contexts, including the Spanish [26, 31].*Previous breastfeeding experiences*: multiparous women will be asked about their experience with breastfeeding while raising previous children, as well as the reason for giving it up.*Type of infant feeding after hospital discharge*: exclusive breastfeeding, nearly exclusive breastfeeding, partial breastfeeding, formula feeding.*Common breastfeeding problems and solutions* (consultation with the midwife, Internet, social networks, reference person …).*Reasons for breastfeeding interruption:* mother’s decision, low weight gain, mother’s disease, newborn’s disease, contraindication due to medication, nipple problems, difficulties with the technique, return to work, etc.***Obstetric outcomes:*** mode of birth (eutocic/dystocic/C-section), mode of start of labour (spontaneous/induced), analgesia during labour (epidural/others), perineal trauma classification (episiotomy/perineal tear degree), initiation of skin-to-skin contact immediately after birth.***Neonatal outcomes:****Perinatal aspects*: newborn’s gender (female/male), weight (expressed in grams), Apgar test score [32], admission in neonatal care unit (yes/no).*Newborn’s health problems in the first 6 months of life:* description for subsequent coding.***Behaviour outcomes:****General Self-Efficacy*: this scale assesses optimistic self-beliefs of coping efficiently with a variety of difficult demands in life. Baessler and Schwarzer’s adaptation [33] will be used, although, in spite of its original format, a ten point Likert-type answer scale suggested by Sanjuan et al. [25] will be used, consisting of 10 items and a scoring range from 10 to 100, with an internal consistency of 0.87 (Alpha coefficient) and a correlation between two halves of 0.88.***Outcomes related to the use of social networks for support:*** frequency of use of social networks and/or WhatsApp, number of times the resource is used, questions resolved through face-to-face appointment in the midwife clinic, use of the App for consultation regarding breastfeeding.

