### Analysis

A complete statistical analysis plan will be previously performed, as well as a report thereof and of the results, according to the Consolidated Standards of Reporting Trials (CONSORT) [35, 36]. The analysis will be carried out on the basis of an intention-to-treat principle, without taking into account whether or not adherence to the breastfeeding support group was completed. Individual health centres are the randomization units and the mother-newborn dyad will be the analysis unit. All statistical trials and confidence intervals will be assumed with a type I error established in alpha = 0.05, using the IBM SPSS V22 statistics package [37].

An exploratory data analysis will be conducted in order to identify atypical values, for the total of our studied sample, as well as for the different sub-groups created. A graphic exploratory analysis of the different studied variables will also be conducted, according to their numerical or non-numerical character. Frequency and percentage distribution scales will be elaborated for the descriptive analysis of variables with a qualitative (non-numerical) character. For the quantitative (numerical) ones, centralization and dispersion measures will be calculated. In variables with a normal distribution, the mean and the standard deviation will be calculated and, in those with an asymmetric distribution, the mean and interquartile range (p25-p75) will be calculated. Furthermore, point estimators and confidence intervals will be calculated at 95% for averages and percentages. The relationship between two qualitative variables will be analysed with Pearson’s chi-square test, the correction for continuity of the chi-square test, a linear-by-linear association test, and Fisher’s exact probability test, based on the application criteria. The significant results of these tests will be complemented with a confidence interval set at 95% for percentage differences.

Regarding the numerical variables between two groups, the Student’s t-test of independent samples for mean comparisons will be carried out, once the requirements of randomness, normality (Kolmogorov-Smirnov’s test, or Shapiro-Wilks’ test, according to the sample size) and equality of variances (Levene’s test) are validated. In case this one is not achieved, the Student’s t-test for independent samples with Welch’s correction will be carried out. In case normality requirements are not accomplished, the Mann-Whitney’s U test will be applied.

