Should any statistically significant differences be considered, confidence intervals at 95% for mean differences will be determined. For the comparison of numerical variables between more than two groups, and once the independence, normality, and homoscedasticity requirements are validated, the ANOVA (analysis of variance) test will be conducted; in case the requirements are not achieved, the Kruskal-Wallis’ test will be carried out. Should any statistically significant differences between the means of the different studied sub-groups be detected, multiple comparison tests will be conducted in order to identify between which sub-groups were those differences found, considering a corrected level of alpha significance based on the number of comparisons made. On the survival analysis, the Kaplan-Meier’s non-parametric estimator will be used.

The effectiveness analysis will be conducted through the comparison of the number of women who chose to breastfeed exclusively at 6 months in both groups, using Fisher’s exact test and estimating the confidence intervals of the difference. Should factors be unequal in both groups, an explanatory logistic regression model would be carried out, in which the dependent variable would be exclusive breastfeeding, and the independent one would be the intervention group, adjusted for the potential factor findings. The efficacy analysis would be carried out on an intention-to-treat basis.

In order to avoid the effect of the intervention on the duration of breastfeeding in the support group, a survival analysis will be conducted, which will compare the intervention and control groups using the log-rank test. Control of potential confounders will be made through Cox’s different regression models. All *p* values under 0.05 will be considered as statistically significant.

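### A normality pre-test picks the test for numerical outcomes, but the only effect measure named is a mean difference, reported only after significance; on the self-efficacy scales the p-value and the estimate can answer different questions

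*Protocol article*

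**What the plan says.** The Analysis section sets one rule for all numerical variables compared between two groups. The default is conditional: "the Student’s t-test of independent samples for mean comparisons will be carried out, once the requirements of randomness, normality" and equal variances have been checked. Normality is judged by "Kolmogorov-Smirnov’s test, or Shapiro-Wilks’ test, according to the sample size" and variances by Levene's test. Unequal variances lead to Welch's correction. Failed normality leads to the rank test: "In case normality requirements are not accomplished, the Mann-Whitney’s U test will be applied".

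The sentence that follows fixes what is reported: "Should any statistically significant differences be considered, confidence intervals at 95% for mean differences will be determined". It makes no exception for the rank test, and no median difference or Hodges-Lehmann shift is named.

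The self-efficacy scales are not named in this rule but fall under it as numerical variables. They serve a specific objective in Methods/design: "Know the influence of these support groups on the perceived self-efficiency of breastfeeding". Under Secondary outcomes measurement the breastfeeding scale is described thus: "It is a one-dimensional, self-completed scale of 14 items, positively presented", and for scoring "it has a Likert-type scale from 1 to 5". The general scale is described as "consisting of 10 items and a scoring range from 10 to 100". Table 1 collects both at baseline and at 2, 4 and 6 months.

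**The concern.** Mann-Whitney tests whether a woman in one arm is equally likely to score above or below a woman in the other. It does not test whether the means are equal. When the two distributions differ in spread or shape, the two questions can have different answers. The plan lets the trial data decide which question the p-value answers, while the only named estimate stays a mean difference.

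Two things can follow for the self-efficacy objective. A significant rank test may be reported beside a mean-difference interval that includes zero. Or the rank test may miss a real gain in the mean, and then the rule provides no interval, so the gain goes unreported. The pre-test also offers little protection: with arms of this size, a comparison of means does not need normally distributed scores.

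**Working it through.** **Arm size.** Study sample size gives 25% in controls, an increase of 12 points (to 37%), two-sided 5% error, 80% power and 10% loss. The usual two-proportion formula without continuity correction gives 232 per arm. 232 × 1.10 = 255.2, rounded up to 256 per arm and 512 in total, which matches the plan. After 10% loss, 256 × 0.90 = 230.4, so about 230 evaluable per arm.

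**Score ranges.** The breastfeeding scale has 14 items scored 1 to 5, so its total runs from 14 × 1 = 14 to 14 × 5 = 70. The general scale runs from 10 to 100. Both are bounded whole-number sums.

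**How often the pre-test fails.** The protocol gives no SD or distribution, so shapes must be assumed. For left-skewed scores rounded to whole numbers on 14-70 (means 54-58, SD 7-12), with 230 per arm, Shapiro-Wilk rejected normality in 100% of simulated samples. For a milder shape (mean 50, SD 8) the normality tests rejected in 78-85%.

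**How often the two methods disagree.** 3,000 simulated trials per row, scaled beta scores rounded to whole numbers, 230 independent women per arm, two-sided 0.05. Mann-Whitney is compared with the Welch interval for the mean difference. A is a significant Mann-Whitney beside an interval covering zero. B is a non-significant Mann-Whitney when the interval would exclude zero.

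| Assumed scenario | Mann-Whitney significant | Welch significant | A | B |
|---|---|---|---|---|
| Same distribution, SD about 9 | 5% | 5% | 1% | 1% |
| Pure shift of 2 points, SD about 9 | 66% | 67% | 3% | 3% |
| Equal means, SD 10 v 8 | 16% | 5% | 13% | 2% |
| Equal means, SD 10 v 7 | 23% | 4% | 21% | 2% |
| Gain of 2 points, SD 10 in both | 71% | 56% | 15% | about 0 |
| Gain of 2 points, SD 10 v 8 | 39% | 64% | 0.1% | 25% |
| 15% low scorers in one arm, mean difference about 0.5 | 70% | 8% | 62.5% | 0.6% |

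Where A was given as a share of significant trials, A = share × Mann-Whitney rate: 0.82 × 16 = 13 and 0.90 × 23 = 21. In rows three to six, B = Welch rate − (Mann-Whitney rate − A): for example 5 − (16 − 13) = 2, and 64 − (39 − 0.1) = 25. Repeat runs moved the significance rates by up to 3 percentage points.

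Total disagreement (A + B) is 2% in the first row and 2-3% across runs with identical distributions. It is 6% for a pure 2-point shift, 15-25% in the next four rows (13% at the low end over repeat runs), and 63% in the last.

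**Would plain Welch do instead?** The Analysis section names health centres as the randomization units, and the table treats women as independent. With an assumed 15 to 25 women per centre and intraclass correlation 0.01 to 0.05, the design effect 1 + (m − 1) × ICC runs from 1 + 14 × 0.01 = 1.14 to 1 + 24 × 0.05 = 2.20. An unadjusted test at 1.96 then has a true critical value of 1.96/√1.14 = 1.84 to 1.96/√2.20 = 1.32, so a false-positive rate of about 7% to 19%. Simulation gave 7-18%.

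**The case against.** Mann-Whitney is a legitimate comparison for a bounded Likert sum, and pairing it with a rank-based estimate would also remove the mismatch. The size of the problem depends on assumed shapes. With identical distributions it is negligible, and the power ranking reverses with the assumption: Mann-Whitney leads 71% to 56% when both arms have SD 10. The protocol announces a complete analysis plan, which could settle the effect measure. The sentence on mean differences can also be read as completing the t-test rule only. All of this is fair and limits the weight of the point. It does not remove it: the protocol states a specific rule, and on the narrower reading the rank branch has no effect measure at all.

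Three stronger readings are tempting and not supported:

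- **That a mean difference is always reported.** The interval is conditional on significance, so only A would appear in the report. In B no interval is planned, which is a loss of power and of information, not a printed contradiction.
- **That a support group which lifts the lowest scorers would produce the printed contradiction.** Nothing in the documents says spread would narrow. When that mechanism is simulated (5 or 8 points added below 45 or 50), A occurs in only 0.1-0.9% of trials. The harm there is missed gains, for example 11% power for Mann-Whitney against 29% for Welch.
- **That Welch's test in every case would be enough.** It would ignore the randomization by centre.

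**Conclusion.** The point stands as a cheap improvement. The rule lets the trial data choose the test, names only a mean difference as the estimate, and gives its interval only after significance. If the self-efficacy totals are skewed, the pre-test will almost always lead to Mann-Whitney at this sample size. The p-value and the estimate then disagree in about 2-3% of trials with identical distributions, 6% under a pure 2-point shift, and roughly 13-25% or more if spread or shape differs. These rates rest on assumed distributions and on independent women.

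A reader might infer that the trial's main conclusion is at risk. It is not. Exclusive breastfeeding at 6 months is a binary outcome analysed by other methods, and the figure of 512 does not depend on this rule. The consequence is confined to the secondary self-efficacy objective and other numerical outcomes.

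**What to change.** For between-arm comparisons of numerical outcomes:

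1. Remove the normality and Levene gates.
2. Pre-specify one mean-difference analysis: a linear model that accounts for health centre as the randomization unit, in preference to plain Welch.
3. Report the mean difference with its 95% confidence interval whatever the p-value.
4. Keep Mann-Whitney as a labelled sensitivity analysis, paired with a rank-based estimate such as Hodges-Lehmann.

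The cost is a rewording of a few sentences, with no change to data collection or sample size. The downside is some loss of power when scores are skewed with equal spread in both arms (56% against 71% in the table's example). The sensitivity analysis would still show the rank-based result.

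### For more than two groups, every failed ANOVA requirement is sent to Kruskal-Wallis, which repairs neither dependence nor unequal variances and departs from the plan's own two-group Welch rule

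*Protocol article*

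**What the plan says.** The Analysis section of the protocol article gives two rules for numerical variables.

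- **Two groups.** The failures are kept apart. If equality of variances is not met, "the Student’s t-test for independent samples with Welch’s correction will be carried out". For the other failure: "In case normality requirements are not accomplished, the Mann-Whitney’s U test will be applied".
- **More than two groups.** The failures are pooled: "once the independence, normality, and homoscedasticity requirements are validated, the ANOVA (analysis of variance) test will be conducted"; and "in case the requirements are not achieved, the Kruskal-Wallis’ test will be carried out". The sentence does not ask which requirement failed.

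A significant result is then described as a difference among sub-group means and followed by pairwise tests, "considering a corrected level of alpha significance based on the number of comparisons made". All tests are run with a "type I error established in alpha = 0.05".

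**The concern.** Three requirements are listed, and Kruskal-Wallis relaxes only one of them, normality. It needs independent observations just as ANOVA does. If the groups differ in spread, its null hypothesis (identical distributions) is false even when all means are equal, so a rejection cannot be read as a difference in means. Yet the protocol reads it that way.

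Comparisons of this kind can arise from the listed variables, for example age or self-efficacy scores across the four feeding categories, or scale scores across schooling or work status. They could feed the specific objective "Determine factors related to breastfeeding sustainment". A factor could be reported as related, or missed, because of how spread and group size happen to pair up, and pairwise tests would follow from that first result.

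**Working it through.** **Inputs from the protocol.** Alpha is 0.05 (Analysis). The planned total is 512 with 10% loss (Study sample size), so about 512 × 0.9 = 460.8 women are analysed. The protocol gives no group sizes, SDs, intracluster correlation (ICC) or centre size for these comparisons. All of these are assumed below.

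**Statistics, with k groups and N women.**
- Kruskal-Wallis: H = 12/(N(N+1)) · Σ Rᵢ²/nᵢ − 3(N+1), where Rᵢ is the rank sum of group i. H is referred to chi-square with k − 1 df.
- Welch's ANOVA: wᵢ = nᵢ/sᵢ², W = Σwᵢ, m̃ = Σwᵢmᵢ/W and t = Σ(1 − wᵢ/W)²/(nᵢ − 1). Then F = [Σwᵢ(mᵢ − m̃)²/(k − 1)] / [1 + 2(k − 2)t/(k² − 1)], on k − 1 and (k² − 1)/(3t) df.

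**Step 1: unequal variances, independent women, normal data, equal means.** There were 6,000 simulated data sets per row. The simulation standard error at 5% is √(0.05 × 0.95/6000) = 0.28 percentage points.

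| Group sizes | SD ratio | Kruskal-Wallis | Welch's ANOVA |
|---|---|---|---|
| 154/154/153 | 1:1:1 | 4.9% | 4.8% |
| 154/154/153 | 1:1.5:2 | 5.8% | 4.9% |
| 154/154/153 | 1:1:3 | 5.8% | 4.4% |
| 300/110/51 | 1:1.5:2 | 10.5% | 5.0% |
| 300/110/51 | 1:2:3 | 12.9% | 5.0% |
| 300/110/51 | 2:1.5:1 | 1.7% | 4.8% |
| 300/110/51 | 3:2:1 | 1.7% | 5.0% |
| 200/150/81/30 | 1:1.3:1.6:2 | 9.7% | 5.2% |
| 200/150/81/30 | 2:1.6:1.3:1 | 2.5% | 5.0% |

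The first row, with equal variances, reproduces the nominal 5%. The rate rises when small groups have the larger spread, falls when large groups do, and stays near 6% with equal sizes.

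**Step 2: four groups on a score scale, SDs 7 to 14, normal data, equal means.** Two assumed splits of 460 women were used. Examples for Kruskal-Wallis (3,000 data sets each):
- 143/46/115/156: SDs 14/7/10/10 give 3.8%; SDs 7/9/11/14 give 4.9%.
- 240/30/80/110: SDs 14/7/10/10 give 2.0%; SDs 14/11/9/7 give 3.9%.

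Over the full set of orderings tried, Kruskal-Wallis runs from about 2% to 11% and Welch's ANOVA from about 4% to 6%.

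**Step 3: dependence.** Centres are randomized and mother-newborn dyads analysed, so women within a centre may be correlated. With four groups, equal variances and 3,000 data sets per row:

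| Grouping factor | Women per centre | ICC | Kruskal-Wallis | ANOVA |
|---|---|---|---|---|
| Constant within centre | 20 | 0.01 | 8.0% | 8.1% |
| Constant within centre | 20 | 0.02 | 11.3% | 12.3% |
| Constant within centre | 20 | 0.05 | 25.1% | 26.7% |
| Constant within centre | 10 | 0.02 | 7.4% | 7.8% |
| Constant within centre | 10 | 0.05 | 14.7% | 15.1% |
| Varies within centre | 10 or 20 | 0.05 | 4.9% to 5.3% | 5.0% to 5.3% |

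The two tests behave almost alike, so switching from ANOVA to Kruskal-Wallis because independence failed gains next to nothing.

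**The case against.** The strongest reply is that this is a generic sentence about secondary comparisons, that a full statistical analysis plan is announced, and that such fallbacks are usually refined there. This lowers the weight of the point but does not remove it. The sentence states a rule, and the rule is wrong for two of its three triggers.

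A reader might also infer more than the document supports:

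- **That false findings exceed 5%.** The direction depends on group sizes and spreads that the protocol does not give. Step 1 has rates near 2% as well as above 10%.
- **That skewed scores make the inflation certain.** Simulated with equal means and unequal SDs, Kruskal-Wallis rejected in about 4% to 15% of data sets under mild skew and about 20% to 42% under strong skew. But the medians truly differ there. For gamma scores of shape 2 centred at the same mean, with SDs 7 and 14, the medians are −1.6 and −3.2, and one group scores higher with probability 0.56. These rejections are false only if the target is the mean. The protocol's reference to means gives that reading some support, but not enough to call the figures a clean false-positive rate.
- **That the rule mishandles the scales repeated at baseline, 2, 4 and 6 months.** Nothing in the protocol applies ANOVA or Kruskal-Wallis across visits. The relevant dependence is between women of one centre. Even that matters mainly for factors aligned with centre, which schooling or feeding type would not be expected to be.
- **That the objective on factors rests on these tests.** The Analysis section also names logistic regression, the log-rank test and Cox models, and does not assign ANOVA or Kruskal-Wallis to that objective.

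**Conclusion.** The point holds as a minor defect of a stated rule. Kruskal-Wallis is a sensible fallback when only normality fails. It is no remedy for failed independence or, if means are to be compared, for unequal variances, and the two-group rule in the same section already treats unequal variances differently.

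The size is an uncontrolled error rate, not a known inflation: about 2% to 11% against a nominal 5% in the four-group normal scenarios with SDs of 7 to 14, and about 4% to 6% for Welch's ANOVA. These figures rest on assumed group sizes and SDs, and the clustering figures on assumed ICCs and centre sizes. The two-arm primary comparison by Fisher's exact test does not use this rule.

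**What to change.** Rewrite the fallback sentence for more than two groups so that each failure has its own remedy:

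- **Unequal variances:** Welch's ANOVA with Games-Howell pairwise comparisons, in line with the two-group Welch rule.
- **Failed normality only:** Kruskal-Wallis, not reported as a difference in means.
- **Women clustered within centres:** a model that accounts for centre, instead of a switch to Kruskal-Wallis.

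It would help to add which rule applies when normality and equal variances both fail. If the mean is the target, Welch's ANOVA stayed at 4.6% to 6.4% in strongly skewed scenarios (gamma, shape 2).

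The cost is a short edit to the Analysis section. The statistical downside is slightly less power than classical ANOVA when variances are in fact equal.

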### Study design

This is a multicentric cluster randomized controlled trial with a control group and an intervention group, without blinding. This protocol has been written according to the recommendations of the SPIRIT 2013 statement [18, 19], a guideline that defines the standard elements of a protocol, including recommendations for intervention trials, which can be found in Additional file 1. Besides, the design of this clinical trial follows the requirements of the CONSORT statement.

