#### Randomization and data management

Centres are randomized to either an intervention arm or normal care. After this randomization, women are allocated either to the intervention group or to the control group by simple random sampling at the 35th–37th week of pregnancy by the midwives at the primary health centres, who will confirm that these women have the intention to breastfeed and that they have indeed initiated it in the first 10 days postpartum. Once the centre randomization for the recruitment of women for the control and intervention groups is conducted, these will be once again randomized following a simple randomization strategy. The participants’ recruitment will begin in September 2020, and will end in March 2022. This will be carried out by those midwives responsible for each health centre, being advised by one of the project’s experts.

These experts will work independently of the accountable researchers for the recruitment of participants. They will allocate health centres using a random sequence made by the *Oxford Minimization and Randomization (OxMAR)* system [23]. The experts will randomly assign a non-transferrable identifier to the health centres, making a difference between the control group and the experimental group centres. Subsequently, each participant will have an identification code depending on their group. This way, we intend to avoid the bias between two women attending antenatal care at the same centre who may or may not join the breastfeeding support group linked thereto, depending on whether they are allocated to one group or the other.

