### Study sample size

Taking into account that the EB rate in Andalusia is 25%, this is considered the expected value in the control group. An estimated increase effect of 12% of the EB rates at 6 months is established, as asserted in previous studies [34]. To reach this difference between both groups, a two-tail hypothesis is set out, with a power of 80% and assuming a type I error of 5%, assuming a loss of 10% in the follow-up, the necessary sample increases to 512 women, 256 in each group. Missing values in the follow-up will be addressed by multiple imputation technique, performing attrition analysis.

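### Health centres are randomised, but the primary Fisher's exact test and the supporting tests treat women as independent, so p-values and confidence intervals can be too favourable

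*Protocol article*

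**What the plan says.** **Allocation.** Study design states: "This is a multicentric cluster randomized controlled trial with a control group and an intervention group, without blinding". Randomization and data management states: "Centres are randomized to either an intervention arm or normal care". The Analysis section repeats the point and names the unit of analysis: "Individual health centres are the randomization units and the mother-newborn dyad will be the analysis unit".

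**Primary test.** The effectiveness analysis in the Analysis section is the "comparison of the number of women who chose to breastfeed exclusively at 6 months in both groups, using Fisher’s exact test", with confidence intervals for the difference. A logistic model is added only if factors turn out unequal between the groups.

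**Other analyses.** Duration is handled by a survival analysis "which will compare the intervention and control groups using the log-rank test", with Cox models for confounders. Other comparisons use chi-square or Fisher tests, independent-samples t-tests or Mann-Whitney tests. No ICC, design effect, centre effect, robust variance or centre-level analysis is mentioned.

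**Missing data.** Under Study sample size: "Missing values in the follow-up will be addressed by multiple imputation technique, performing attrition analysis".

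**Conflicting wording.** Randomization and data management also says that "women are allocated either to the intervention group or to the control group by simple random sampling at the 35th–37th week of pregnancy", and the abstract likewise speaks of simple randomisation of women. The same section gives the purpose of allocating centres: "we intend to avoid the bias between two women attending antenatal care at the same centre".

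**The concern.** Analysing dyads in a cluster trial is legitimate, but only with a method that allows for the correlation between women of the same centre. Fisher's exact test on pooled counts does not. It compares the arms as if each woman had been allocated separately.

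Correlation within centres is plausible here. Women at an intervention centre attend the support group linked to that centre, with monthly midwife-led sessions and shared Facebook and WhatsApp groups, and the sessions are designed so that mothers influence one another. Centres may also differ in population and practice.

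If that correlation is ignored, standard errors are understated. A significant primary result could then reflect chance differences between centres rather than the support groups. The Discussion says the results will help produce a guide for other centres, so a false positive would have practical consequences.

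**Working it through.** **1. Does the sample size allow for clustering?** Inputs from Study sample size: 25% in the control group, an increase of 12 points (so 37%), two-sided alpha 0.05, power 80%, 10% loss.

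- Variance term: 0.25 × 0.75 + 0.37 × 0.63 = 0.1875 + 0.2331 = 0.4206.
- n per arm = (1.960 + 0.842)² × 0.4206 / 0.12² = 7.85 × 0.4206 / 0.0144 = 229.3, so 230.
- With 10% loss: 230 / 0.90 = 255.6, so 256 per arm and 512 in total.

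This is exactly the stated figure. It comes from the formula for individually randomised women, with a design effect of 1.

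**2. True type I error of the planned primary test.** The article gives no ICC, number of centres or women per centre, so these are assumptions. The simulation was beta-binomial with 20,000 trials per setting, a true rate of 25% in both arms, about 230 analysed women per arm spread over half the centres, and a two-sided Fisher test at 0.05.

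| Total centres | ICC 0.01 | ICC 0.02 | ICC 0.05 |
|---|---|---|---|
| 40 | 4.8% | 5.6% | 9.0% |
| 20 | 6.5% | 8.7% | 15.7% |
| 10 | 8.7% | 13.7% | 25.4% |

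With no clustering, Fisher's test runs at about 3.9%, which is its usual conservatism. A second simulation with 12 centres of 20 women per arm (24 in all) gave 5.9%, 8.1% and 14.3%, in line with the middle row.

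**3. Check by formula.** The design effect is DE = 1 + (m − 1) × ICC, where m is the number of women per centre. The true level of a nominal 5% z-test is 2 × [1 − Φ(1.96 / √DE)]. For 20 centres, m = 230 / 10 = 23. At ICC 0.02, DE = 1 + 22 × 0.02 = 1.44 and √DE = 1.2, so the level is 2 × [1 − Φ(1.633)] ≈ 10%. The simulated 8.7% is a little lower, as expected from Fisher's conservatism. The unadjusted confidence interval would be 1 / 1.2 = 0.83 of its proper width.

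**4. Power once clustering is respected.** Take m = 20 and ICC 0.02, so DE = 1 + 19 × 0.02 = 1.38. The effective size is 230 / 1.38 ≈ 167 per arm.

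- Power = Φ([0.12 × √167 − 1.96 × √(2 × 0.31 × 0.69)] / √0.4206) = Φ([1.55 − 1.28] / 0.649) ≈ 66%.
- With m = 10 and ICC 0.01 the same formula gives 76%. With m = 20 and ICC 0.05 it gives 51%.

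**The case against.** **The analysis plan may deal with it.** The article promises a full statistical analysis plan, and an article need not list every modelling detail. But this is not a detail left open. The article names the primary test, and a later plan would have to contradict it to repair the problem.

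**Women may be the randomised units.** The text on simple randomisation of women, read alone, describes individual allocation. If women were truly allocated within centres, the type I error figures above would not apply. Study design, the sentence on randomisation units and the stated aim of not mixing arms within a centre all favour centre-level allocation. The concern stands, but it depends on that reading, and the article must settle it.

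**Fisher's test is conservative.** This is true, and it matters with many centres and a small ICC: at 40 centres and ICC 0.01 the error rate is 4.8%. A reader might infer that the results will necessarily be too favourable. The documents do not support that, because they give neither the ICC nor the number of centres.

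**Multiple imputation.** A reader might also infer that Fisher's test and the planned imputation cannot be run together. That goes too far. The same sentence of the Analysis section calls for confidence intervals of the difference, and a difference in proportions with its standard error can be pooled by Rubin's rules. What remains is narrower: the Fisher p-value itself has no standard pooling rule.

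**A single shared midwife.** It is tempting to say that all women of a centre share one midwife. The article speaks of a reference midwife and of the midwives responsible for each centre, but gives no number per centre. The argument does not need it.

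**Conclusion.** Wrong as written. With centres as the randomised units, the primary test and the log-rank, chi-square and t-tests rest on an independence assumption that the design does not justify. The regression models share the gap as described.

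The size is conditional. For ICCs of 0.01 to 0.05, the real type I error of the primary test is about 5–9% with 40 centres, 6–16% with 20 and 9–25% with 10. In the most favourable corner there is no inflation, but nothing in the article places the trial there. The conclusion assumes centre-level allocation and some positive correlation within centres.

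**What to change.** - **Primary analysis.** Replace Fisher's test with an analysis that accounts for centre. Examples are GEE or a mixed-effects logistic model with centre as the cluster and a small-sample correction, or a centre-level analysis if centres are few. Choose one before outcome data are seen. Report the risk difference with a cluster-adjusted 95% confidence interval; a mixed logistic model does not give it directly, so state how it is derived.
- **Other analyses.** Account for centre in the same way for duration (for example a Cox model with shared frailty or cluster-robust variance) and for the self-efficacy scales (for example a linear mixed model).
- **Missing data.** Include centre in the imputation model and pool the model estimates by Rubin's rules.
- **Text.** Reconcile the wording on simple randomisation of women, in the abstract and in Randomization and data management, with centre-level allocation. State the number of centres and the assumed ICC.

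**Cost.** No new outcome data are needed. Centres receive an identifier, but the article says participants' codes depend on their group, so confirm that each woman's centre is kept in the database. The larger cost is precision. Intervals will be wider, and 512 women will not deliver the stated 80% power if outcomes are correlated: about 66% with 20 women per centre and ICC 0.02, both assumed. Either the sample size is revisited with a design effect, or the lower power is acknowledged.
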